**3. Randomisation**

If a participant meets all the study criteria, then they will be randomised to either an immediate treatment group or a waitlist control group (WLC). Randomisation will be conducted using a random number generator via the website www.random.org to ensure unbiased selection. Assessing clinicians will not be aware of the randomisation status of participants and will be advised of their participants’ group randomisation by the Principal Investigator. Participants will be advised of their group assignment, along with their acceptance into the study, via email. An email with a REDCAP link to pre-treatment questionnaires will be sent to participants in both groups to be completed. After the competition of these questionnaires, participants in group 1 (immediate treatment) will be called to schedule treatment to begin as soon as possible. Participants in group 2 (waitlist control) will be called 9 weeks later to complete the diagnostic interview and self-report questionnaires and schedule treatment as soon as possible.

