**4. Questionnaire Administration (pre-treatment, post-treatment, follow-up)**

All participants will complete the symptom screeners online via REDCAP before starting treatment (pre-treatment), after treatment completion (post-treatment), and three months after treatment (follow-up). These questionnaires will be automatically emailed via REDCAP at the allocated time. It is anticipated that it will take 20 minutes to complete the self-report questionnaires at each time point.

The diagnostic interview (DIAMOND) will be administered at post-treatment and follow-up via phone or videoconferencing (and before commencing treatment for the control group). Participants will be contacted to schedule this appointment, and ideally this appointment will be scheduled in the final treatment session. Only the modules that the participants met criteria for at pre-treatment will be administered.

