**TREATMENT**

Wherever possible, treatment and assessment will be provided by separate therapists. Treatment will be delivered by provisional and registered psychologist(s) under the supervision of a board-approved supervisor on the research team.

Provisional psychologists will be UTS Master of Clinical Psychology students on their clinical placement, meaning that treatment and assessment sessions delivered will count toward their clinical hour count as part of their placement. Before new provisional psychologists begin delivering treatment, an amendment will be submitted to the MREC to advise of the addition. All new clinicians who will provide the treatment will receive a 1–2-hour training session delivered by [name]. All sessions will be recorded to ensure treatment fidelity, and 10% of these sessions or more will be reviewed by an investigator.

Treatment will be delivered remotely, via videoconferencing on Zoom. Zoom has been selected as the telehealth program of choice due to its compliance with the HIPAA requirements for healthcare (Zoom, 2021) and its availability to the researchers through a University of Technology paid licence with UTS-affiliated information technology and security support. Zoom meets its confidentiality in healthcare needs by encrypting data in motion at the layer of the application using Advanced Encryption Standard (AES) (Zoom, 2021). The clinicians delivering treatment in the study can easily control Zoom privacy settings to prevent unauthorised access by ensuring that all meetings are password protected and using waiting rooms. As meeting hosts, clinicians in the study have the capability to easily remove participants from meetings, which are only available through a privacy-protected link available only to the client and clinician. Participants are informed of and agree to the privacy limitations of accessing treatment in the Participant Information and Consent Form. Previous teleconferencing delivered treatment protocols with ethics approvals have used Zoom as their medium of choice to deliver CBT for anxiety disorders (Trenoska Basile et al., 2022; Winter et al., 2023). Archibald et al. (2019) found that out of 16 healthcare providers qualitatively interviewed via Zoom, most participants rated Zoom more positively than in-person or other videoconferencing platforms due to its security options, cost-effectiveness, and features that support data management.

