**ANALYSIS PLAN**

To meet the study’s aim (i.e., to understand if the treatment is efficacious for reducing symptoms of anxiety disorders ), the following analyses will be conducted. The main analyses looking at treatment outcomes from the RCT will be carried out using conservative intention-to-treat principles and using mixed-linear models analyses to handle missing data. Mixed-models are a robust statistical approach for analysing longitudinal clinical trial data and these analyses will employ an appropriate covariance structure and maximum likelihood estimation, which provides unbiased estimates in the case of missing data, under the assumption that data is missing at random. These analyses account for the effect of missing data, thus additional participant recruitment to account for drop-out rates is not warranted. Using this dataset, other appropriate analyses arising from secondary papers will also be conducted. Participants have been informed in the PICF that other secondary data analyses will be conducted on the data that they provide during their participation in the research trial. This may include intersectional moderator analyses of treatment efficacy based on person-level stigma moderators from the minority stress model to inform further treatment adaption needs (Barrera & Castro, 2006; Meyer, 2003). Comparisons between the standard treatment and the LGBTQ-affirmative CBT protocol will be compared using benchmarking analyses (Minami et al., 2008).

To understand the treatment’s efficacy, clinically significant change will be measured using three methods. Diagnostic change will be assessed from pre- to post-treatment and at follow-up using the DIAMOND structured interview. Treatment response will be measured using the reliable change index (RCI) of Jacobson and Truax (1991) to understand which change on the OASIS is not attributable to measurement error, but rather is statistically reliable. Any increase in symptoms by the RCI magnitude of change will be defined as deterioration in this trial. Clinically significant change at post-treatment and to follow-up will be defined as a score below the cut score of 8 on the OASIS (Campbell-Sills et al., 2009).

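### The protocol both blinds assessing clinicians and has them told the allocation, so blinding of the week-9 DIAMOND and clinician-rated CGI-S is contradicted and not secured

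*Protocol*

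**What the plan says.** Section 3 (Randomisation) holds the Protocol's only statement on what assessors know about allocation: "Assessing clinicians will not be aware of the randomisation status of participants and will be advised of their" participants' "group randomisation by the Principal Investigator". The two halves of the sentence share one subject: the first says that these clinicians are unaware, the second that they "will be advised of their participants’ group randomisation by the Principal Investigator".

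Other sections bear on who rates outcomes and in what setting:

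- Treatment: "Wherever possible, treatment and assessment will be provided by separate therapists".
- Section 4 (Questionnaire Administration), on the post-treatment DIAMOND: "ideally this appointment will be scheduled in the final treatment session".
- Section 3, on the waitlist group: its members "will be called 9 weeks later to complete the diagnostic interview and self-report questionnaires and schedule treatment as soon as possible".
- Table 1: the DIAMOND and the clinician-assessed CGI-S fall at week 9 in both groups. The column is labelled as post-treatment for Group 1 and pre-treatment for Group 2.
- Analysis Plan: "Diagnostic change will be assessed from pre- to post-treatment and at follow-up using the DIAMOND structured interview". This is the first of three methods for clinically significant change.
- Participant Numbers & Power: diagnostic status has its own sample size, 42 participants.

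**The concern.** Who is told the allocation, and when, is a matter of trial conduct that the protocol has to settle, and here it settles it both ways. A site could follow either half of the sentence and claim compliance. A later report could describe blinded diagnostic assessment that the text does not support.

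This matters because participants are emailed their group and the comparator is a waitlist, so self-report outcomes cannot be masked. The DIAMOND and the clinician-rated CGI-S are the efficacy measures for which masking the rater is possible. Both call for judgement, and a rater who knows that one person has just finished therapy and another has been waiting may resolve borderline cases differently. Any such tendency would enter the between-group comparison of diagnostic status directly.

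**Working it through.** **1. Does any reading of the sentence secure blinding at week 9?**

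- Literal reading: assessors are unaware and are told. The two halves cannot both hold.
- Sequential reading: assessors are unaware at the eligibility interview and told after randomisation. This removes the contradiction, but those assessors then know the arm before week 9.
- Slip of the pen: treating clinicians, not assessors, were meant to be told. The sentence is then wrong as written and needs correcting.

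No reading of the current text secures an uninformed rater at week 9. The rest of the Protocol does not supply one: separation of therapist and assessor is qualified, and the week-9 interviewer is not identified.

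**2. Which outcomes are exposed?** From Table 1 and the Analysis Plan:

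| Outcome | Rater | Week-9 comparison of both groups? | Exposed? |
|---|---|---|---|
| DIAMOND diagnostic status | clinician | yes | yes |
| CGI-S (assessed) | clinician | yes | yes |
| CGI-I (assessed) | clinician | no, Group 1 only | no between-group comparison |
| OASIS, its reliable change index and its cut score of 8 | participant | yes | no |

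**3. The plan's own figure for diagnostic status.** Inputs from Participant Numbers & Power: remission 55.8% with CBT, 15.4% on waitlist, alpha 0.05 (taken as two-sided), 80% power. The mean proportion is (0.558 + 0.154)/2 = 0.356.

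n per group = [1.96·√(2·0.356·0.644) + 0.8416·√(0.558·0.442 + 0.154·0.846)]² / (0.558 − 0.154)²
= [1.327 + 0.517]² / 0.1632 = 20.8, so 21 per group and 42 in total.

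The stated figure reproduces without a continuity correction (power 0.803 at 21 per group). No figure in the plan is in dispute.

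**4. Illustration of size, by assumption only.** The documents give neither a rating bias nor the test for diagnostic status. I assumed:

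- 26 per arm, no true effect, and true remission p of 15.4%, 25% or 35% in both arms;
- ratings that raise the treated arm alone by δ;
- a pooled two-sided z-test at 0.05.

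The false-positive rate is the sum of Bin(a; 26, p + δ)·Bin(b; 26, p) over all pairs (a, b) for which |a − b|/26 divided by √(2·p̂(1 − p̂)/26) exceeds 1.96, where p̂ = (a + b)/52.

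| True remission | δ = 0 | δ = 5 points | δ = 10 points |
|---|---|---|---|
| 15.4% | 5.6% | 8% | 15% |
| 25% | 5.5% | 7% | 13% |
| 35% | 5.5% | 7% | 12% |

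The level depends on the test. The same enumeration with Fisher's exact test starts at 2% to 3% and rises to 3% to 4% (5 points) and 7% to 8% (10 points). The direction is the same.

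**The case against.** The strongest reply is that the sentence sits directly after the eligibility interview and is about allocation concealment: the eligibility assessor does not know the arm and learns it afterwards. That is a natural reading and removes the contradiction. It does not secure blinding at week 9, but it does show that the text need not be an admission that outcome raters are informed.

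A reader might therefore be tempted to go further than the documents allow, in four ways:

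- **That the week-9 ratings are unblinded.** The Protocol does not say who conducts that interview, so this is an inference that adopts one half of a contradictory sentence.
- **That one pool of clinicians both treats and assesses, or that the therapist does the interview.** Separation is the stated default, no common pool is defined, and the remark about the final treatment session can simply mean that the appointment is booked then.
- **That clinician CGI as a whole is affected.** Only the assessed CGI-S is scheduled at week 9 in both groups.
- **That false-positive rates could reach 56%.** Such figures need ratings to move up in one arm and down in the other. With 5 points each way the rate is 13% to 18%, and with 10 points each way 34% to 56%. At 15.4% remission the latter means 25.4% against 5.4%. Nothing in the Protocol supports opposite shifts of that size.

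It is also fair to say that the trial is described as a feasibility study with exploratory power, that its primary outcome is self-reported, and that participants may reveal their arm whatever is written. These points limit the consequence. They do not reconcile the sentence.

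**Conclusion.** The point holds in a limited form. The Randomisation section contradicts itself on whether assessing clinicians know the allocation, the Treatment section does not guarantee a separate assessor, and no passage names an uninformed week-9 rater. Blinding of DIAMOND diagnostic status and clinician-assessed CGI-S is contradicted and not secured; whether the ratings would in fact be unblinded cannot be established from the text.

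The OASIS primary analysis and two of the three clinically-significant-change methods are untouched. The 42-participant calculation is arithmetically sound. The illustrated inflation, from about 5.5% to 7% to 8% or 12% to 15%, rests on an assumed one-arm rating bias of 5 or 10 points and a z-test that the Protocol does not specify. It shows direction and rough scale and is not an estimate for this trial. The matter should be corrected because it touches a separately powered outcome and is cheap to put right.

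**What to change.** Amend the sentence in section 3 (Randomisation) so that the Principal Investigator tells only the treating clinician and scheduling staff the allocation. State that the week-9 DIAMOND and CGI-S will be done by an existing study clinician who is not that participant's therapist and has not been told the arm, and that any unblinding will be recorded. Where this cannot be arranged, report those ratings as unblinded.

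The cost is a short change of protocol text and less flexible rostering. Since separation of treatment and assessment is already the stated aim, the change firms up an existing intention. The Protocol gives no staffing numbers, so the sponsor should confirm that enough clinicians are available.

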**4. Questionnaire Administration (pre-treatment, post-treatment, follow-up)**

All participants will complete the symptom screeners online via REDCAP before starting treatment (pre-treatment), after treatment completion (post-treatment), and three months after treatment (follow-up). These questionnaires will be automatically emailed via REDCAP at the allocated time. It is anticipated that it will take 20 minutes to complete the self-report questionnaires at each time point.

The diagnostic interview (DIAMOND) will be administered at post-treatment and follow-up via phone or videoconferencing (and before commencing treatment for the control group). Participants will be contacted to schedule this appointment, and ideally this appointment will be scheduled in the final treatment session. Only the modules that the participants met criteria for at pre-treatment will be administered.

**5. Qualitative Interview**

Eight to ten participants from both group one and group two (after commencing treatment), with a total of 16 – 20 participants, will be selected for inclusion to the qualitative interview, consistent with sample size in this area of the research (Jackson et al., 2022; Pachankis et al., 2020). Participants who consent to be interviewed in their initial PCIF will be selected based on a representative matrix that aims to achieve a maximally diverse sample, as per previous studies (Christensen et al., 2023). Wherever possible, a member of the research team who did not conduct the participant’s treatment will conduct the interviews. Masters students who conduct the interviews will be supervised by members of the research team.

The interview scheduled for a time that suits participants after the diagnostic interview and is expected to take approximately 30 to 60 minutes. For those who drop out or do not attend regular appointments, they will be still be contacted to organise an appointment time that suits them if they would like to participate. Field notes will be written immediately after each interview and organised as observational notes, theoretical notes, methodological notes, and analytical memos as suggested by Groenewald (2004). The interview topic guide is available in Appendix L, with support services to be provided to participants after the interview in Appendix M. The interview topic guide was derived from review of previous literature on evaluating acceptability in clinical trials (Sekhon et al., 2017), and from LGBTQ-adapted CBT specific trials (Jackson et al., 2022) and will be refined throughout the study as required as is best practice in qualitative research.

Interview audio will be recorded to assist with transcription. The benefits of the feedback on the intervention will be discussed at the beginning of the interview to encourage candid feedback in the semi-structured interview. Framework analysis (Ritchie & Spencer, 1994) will be used to analyse data under acceptability domains raised in the topic guide along with any additional inductive coding. Coding will be completed by the student investigator in a collaborative process with other investigators.

Design and reporting of the study will be guided by relevant guidelines, including the Consolidated Criteria for Reporting Qualitative Research (COREQ) (Tong et al., 2007). Strategies to maximize the trustworthiness of the research (Lincoln & Guba, 1985) will be employed (e.g., member checking, presentation of data verbatim, reflexive diarising and discussion).

**6. Managing Study Procedure Risks**

We expect participants will experience clinically significant improvements in the symptoms of their anxiety disorder. We also hope that participants will apply the strategies learnt in this trial after study completion, which will likely lead to long-term management of their symptoms. The protocol for treatment encourages participants to not just learn but practice techniques to manage their mental health conditions’ symptoms. It is important to note that in the short-term, participants in cognitive behavioural therapy can experience an increase in symptoms of a mental health condition; however, this is only a temporary increase and will diminish as treatment progresses (Reinecke et al., 2018).

At pre-treatment, post-treatment, and follow-up, participants will be given the option to choose whether their health care provider(s) are made aware of their participation in the study. The templates for these letters are available in Appendix N.

Supporting participant’s safety and emotional well-being is a priority of the researchers. In the rare circumstance that someone requires psychiatric consideration or experiences significant distress, the investigators are mental health clinicians who can assess the situation and refer the person to appropriate services such as their primary physician or emergency services. Given that this study is not trialling the effects of a pharmaceutical drug or medical equipment but rather the effects of talk therapy, potential adverse events are rare. In the unlikely event that adverse events do occur, a log will be kept of adverse events that arise. Serious adverse events (SAEs) involving an immediate physical risk to participant safety will be reported to the Principal Investigator, who will advise the Human Research Ethics Committee of the nature of the SAE and any actions taken to mitigate its effects.

It is noted by the researchers that most people presenting for treatment with an internalising disorder have experienced their symptoms for several years (Patton et al., 2014). This means that participants have likely consulted multiple medical or mental health clinicians without complete or partial remission of symptoms. Minority stressors for LGBTQ+ participants are also by nature managed by LGBTQ+ people chronically in the long-term (Meyer, 2003), and thus unlikely to need urgent care within the eight-week period of the waitlist, while receiving treatment for eight weeks, or during follow-up. In any case, this study is not a crisis service, and participants who need urgent care will be referred out at assessment to seek urgent psychiatric care or support from their primary care provider.

Management of risk will be ongoing throughout the project. Importantly, all participants will be made aware of what steps they can follow in a mental health emergency in multiple communication modes at multiple timepoints. For example, which services to contact and what to do in a mental health crisis is outlined in (1) the PICF; (2) a safety plan provided to all clients at the beginning of treatment; (3) in every email communication with participants. Secondly, participants' responses to their questionnaires will be monitored, meaning that deteriorating or consistently elevated symptoms will trigger the research team to contact the participant to encourage contact with their health care team or emergency services. All communication between participants and the research team will be documented.

Assessed for eligibility.

Participants who do not meet criteria will be excluded.

Three-month follow-up diagnostic assessment.

Post-treatment diagnostic assessment and self-report questionnaires.

Qualitative Interviews (n = 10)

Allocated to immediate intervention with Unified Protocol (n = 26).

Post-treatment diagnostic assessment and self-report questionnaires.

Qualitative Interviews (n = 10)

Three-month follow-up diagnostic assessment.

## Allocation

## Follow-up

## Post-treatment

Randomized (n = 52)

Analysed

Analysed

## Analysis

Treatment phase

**Figure 1.**

*Study Flow Diagram*

Pre-screened for eligibility.

Participants who do not meet criteria will be excluded.

Allocated to waitlist control condition with LGBTQ-Affirmative Unified Protocol after 9-week waitlist period ends (n = 26).

Diagnostic status and self-report measures re-administered prior to treatment.

**STUDY MEASURES**

***Online Screening Measures***

The questionnaires that participants will complete for eligibility screening in REDCAP are outlined below, and are shown in detail in Appendix P.

- **Demographic Form:** A basic demographic questionnaire will collect information on age, location, gender identity, sexual orientation, marital status, employment and education status, racial identity, access to a computer in a private space, and medication use.
- **DIAMOND Screener:** The DIAMOND screener (Tolin et al., 2018) is a 30-item self-report questionnaire which is used to indicate to the clinician which modules of the DIAMOND need to be administered during the semi-structured diagnostic interview. Only items endorsed on the DIAMOND screener are delivered during the DIAMOND interview.
- **Risk Questionnaire:** This risk questionnaire is a standard five-item questionnaire used to assess risky behaviours such as deliberate self-harm and problematic alcohol and/or illicit drug use. It has been used in online treatment studies (Wootton et al., 2019a) to screen for participants whose risk level may be too high to be seen in a remote treatment setting.
- **Patient Health Questionnaire 9-Item (PHQ-9) (Kroenke et al., 2001):** The PHQ-9 is a 9-item measure of depressive symptoms. Participants rate how frequently they experienced each symptom in the past two weeks on a four-point Likert scale from zero (*not at all*) to three (*nearly every day*). Scores of 10 or greater indicate clinically significant depression symptoms (Manea et al., 2012). The PHQ-9 has been demonstrated to have good psychometric properties in previous studies (Kroenke et al., 2001; Zuithoff et al., 2010).

